### Sample size and power calculation

Based on previous research, we expect approximately 4% of current smokers seen with usual care conditions will report having quit smoking at 6 months after a baseline visit (32). This is based on a model whereby 20% of current smokers discuss a quit attempt (higher than usual with Hawthorne effect) (11), 10% get a specific pharmacologic aid or e-cigarette, and 4% successfully quit. We anticipate a 100% increase in the number of quit discussions in the intervention arm, so about 40% of current smokers discuss a quit attempt. Subsequently, 20% will use a pharmacologic aid or e-cigarette, and 10.5% will successfully quit. For the primary outcome will use mixed effect models accounting for clustered, repeated measures; without adjusting for baseline patient characteristics, we will compare two proportions, using a two-sided test for significance, β = 0.80, α = 0.05, and an intraclass correlation coefficient of 0.03. With these parameters, we need 20 clusters (i.e. individual GPs) in each arm, each with 20 current smokers who consent to inclusion. Assuming 15% drop-out or under-recruitment by individual GPs, we will aim to recruit 46 GPs with 23 patients each, so 1,058 patients. Individual GPs will be capped at 25 patients. No specific interim or safety analyses are planned. STATA version 16.0 for Windows (StataCorp LLC, College Station, USA) will be used for all statistical analyses. Stopping rules for the study: Recruitment of GPs will end when 46 have signed a contract to complete the training program and undergone randomization. Patient recruitment will end when all participating GPs have included ≥ 20 patients and 1,060 patients have been recruited overall. GPs will be considered inactive if they have not recruited patients within the last 6 months. The trial will also end if GP recruitment has ceased and all GPs have completed recruitment. If recruitment is too low (< 200 patient participants 12 months after beginning GP training programs), new recruitment strategies will be put in place and the study may be terminated.

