### Study procedures

During the recruitment period, the study team will proactively contact GPs to ensure that patient enrolment is going as planned. The GPs will also complete questionnaires at the end of patient recruitment (T1, approximately 6 months after training) and at the end of patient follow-up (T2, approximately 12 months after training). Figure 2 shows the diagram of what is expected by GPs. Moreover, all GPs will also be asked in the T1 questionnaire to participate in a 30-min optional semi-structured interview (see interview guide in Additional file 1; Appendix Table 1). We will perform 10 to 15 interviews, and analyze transcripts using a process evaluation methodology to understand how GPs approach smoking cessation with their patients and how that changed when using default choices and an electronic decision aid.

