### Withdrawal and discontinuation

Patient and GP participants can withdraw from the study at any time. Only baseline anonymised information will be retained for analysis once the patient/GP withdraws. If a GP withdraws, his or her patients can still be followed-up individually until the end of the study.

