#### Handling of missing data and drop-outs

For the primary outcome, participants lost to follow-up will be considered as continuing smokers. We do not plan to replace drop-outs as the sample size calculation anticipates a 15% under-recruitment / dropout rate. Imputation will not be done for other variables of interest (weight, laboratory data). Participants lost to follow-up will be considered as continuing smokers without quit attempts/quit aids. For other secondary outcomes, data will be considered missing completely at random. The primary analysis will be an intention to treat analyses, with participants analysed according to their study arm, regardless of the completion rate. Participants lost to follow-up will be considered as continuing smokers.

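### Treating GP uptake of the opt-out behaviours as missing completely at random is unjustified; if GPs without data adopt less, a responders-only uptake figure will be too high

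*Protocol article*

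**What the plan says.** The section Handling of missing data and drop-outs sets two rules for secondary outcomes. For quit attempts and quit aids, a lost participant is counted as a failure: "Participants lost to follow-up will be considered as continuing smokers without quit attempts/quit aids". For everything else: "For other secondary outcomes, data will be considered missing completely at random".

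GP uptake (offering quit aids to all current smokers, and using the decision aid) is the fourth secondary objective under Objectives and appears again under Secondary outcome measures. Nothing exempts it from the second rule. The intention-to-treat sentence in the missing-data section refers to the primary analysis only, so it does not fix a denominator for GP uptake.

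Three other places bear on the point:

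- Study procedures has GPs complete questionnaires about 6 months (T1) and about 12 months (T2) after training.
- Withdrawal and discontinuation limits what is kept after a withdrawal: "Only baseline anonymised information will be retained for analysis once the patient/GP withdraws". It then adds: "If a GP withdraws, his or her patients can still be followed-up individually until the end of the study".
- The same missing-data section says of drop-outs: "We do not plan to replace drop-outs as the sample size calculation anticipates a 15% under-recruitment / dropout rate".

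**The concern.** Missing completely at random means that whether a GP supplies data is unrelated to whether that GP took up the behaviour. That is hard to defend here. The training asks GPs to change how they consult, and those who lose interest in the trial are plausibly those who did not change. The article itself expects uneven engagement: Controlling for contamination and other potential biases foresees under-recruitment by certain GPs, and Sample size and power calculation has a category of inactive GPs. Blinding concedes that GPs may notice how their training differs, so loss could also differ by arm.

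Uptake matters because the theoretical framework (caption to Fig. 4) puts the change in GPs' approach ahead of quit attempts and cessation. The Discussion also allows that the intervention may be too weak to show an effect. If the primary result is null, uptake helps to separate an approach that was not delivered from one that was delivered and did not work. An uptake figure that is too high would push readers towards the second explanation.

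**Working it through.** **Inputs from the article.** There are 46 GPs, so about 23 per arm if split equally. The allowance reads: "Assuming 15% drop-out or under-recruitment by individual GPs, we will aim to recruit 46 GPs with 23 patients each, so 1,058 patients". The total agrees (46 × 23 = 1,058). No expected uptake and no GP questionnaire non-response rate is given, so there is no figure of the plan's own to reproduce on this point.

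**Assumed inputs.** Uptake among responding GPs, c: 40%, 60% or 80%. Share of GPs with no post-training data, d: 5%, 15% or 30%. Uptake among missing GPs, u: zero, or half of c.

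**Formula.** Uptake over all randomised GPs is c(1 − d) + u·d. An analysis that assumes missing completely at random reports c. The error is therefore

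c − [c(1 − d) + u·d] = d(c − u).

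**Size in one arm.** For c = 60% and d = 15%:

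- u = 0: 0.15 × (60 − 0) = 9 points; all-GP uptake is 51%.
- u = 30%: 0.15 × (60 − 30) = 4.5 points; all-GP uptake is 55.5%.
- u = 60%: 0 points; the assumption is then harmless.
- u = 100%: 0.15 × (60 − 100) = −6 points; uptake is understated.

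Overstatement in points for c = 40 / 60 / 80%:

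| Share missing | u = 0 | u = half of c |
|---|---|---|
| 5% | 2 / 3 / 4 | 1 / 1.5 / 2 |
| 15% | 6 / 9 / 12 | 3 / 4.5 / 6 |
| 30% | 12 / 18 / 24 | 6 / 9 / 12 |

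**In whole GPs.** With 23 in an arm, 60% among responders and no uptake among the missing: 3 missing gives 0.60 × 20/23 = 52%; 4 missing gives 0.60 × 19/23 = 50%.

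**Between arms.** Assume responder uptake of 60% (intervention) and 30% (control), a difference of 30 points. Counting missing GPs as non-adopters gives:

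- 15% missing in both arms: 51 − 25.5 = 25.5 points.
- 25% intervention, 10% control: 45 − 27 = 18 points.
- 10% intervention, 25% control: 54 − 22.5 = 31.5 points.

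So the responders-only difference may be too large or too small, depending on which arm loses more GPs.

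**The case against.** The case for leaving the plan alone has several parts, and some of it stands.

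- **The source of the uptake measure is not fixed in the article.** The T1 and T2 questionnaires have stated times, but nothing says that uptake is read from them. The measures are set out in Appendix Table 4, which is not shown. Patients could report whether a quit aid was offered or the decision aid used, and patients of a withdrawn GP can still be followed. This stands: to the extent that uptake is patient-reported, the loss is smaller. It would not help for a GP who left before enrolling anyone.
- **The missing-data section does not name GPs.** Its specific content is about patients, and patients' perceived involvement is an obvious target of the second rule. That is fair, but GP uptake is a secondary outcome too, and no other rule is offered for it.
- **The 15% is not a GP non-response rate.** A reader might infer that 15% of 23, or 3 to 4 GPs per arm, will be missing. The article does not support that. Its phrase is "Assuming 15% drop-out or under-recruitment by individual GPs", which mixes two things, and a GP who recruits too few patients can still return both questionnaires. GPs are also under contract, reimbursed and contacted regularly. Here 15% serves only as an illustration.
- **Partial data are not all lost.** Statistical methods plans mixed-effect models for repeated outcomes, under which a GP with T1 but not T2 still contributes. This stands for non-response. It does not stand for withdrawal, where the text keeps baseline data only.
- **Delivery can be judged in other ways.** Quit attempts, quit-aid use, perceived involvement and the interviews also inform it. This lowers the stakes but does not make the stated assumption right.
- **Counting missing GPs as non-adopters is itself an untestable assumption.** This stands, and the between-arm figures show how it can distort the contrast when loss differs. It argues for a sensitivity analysis, not for a new main analysis.

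**Conclusion.** The point holds in conditional form. The article chooses the assumption outright and gives no reason for it. As worded it reaches GP uptake, where it is implausible. This is a weak rule that has been stated, not a detail left to a later plan.

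A reader might go further and conclude that uptake will be overstated. The documents do not show that. Overstatement requires two things: that uptake comes from data that a lost GP no longer supplies, and that lost GPs adopt less than responders. On the illustrative inputs of 60% uptake and 15% missing, the overstatement runs from 0 to 9 points as uptake among the missing falls from the responders' rate to zero. With 5% missing, the upper end is 3 points; with 30%, it is 18. No direction can be claimed for the between-arm difference.

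Nor does the rule for lost patients contradict the rule for GPs. Counting lost smokers as still smoking is a convention for a patient outcome, and the article is free to treat GP behaviour differently. The matter is a modest improvement to one secondary outcome and leaves the primary analysis untouched.

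**What to change.** In Handling of missing data and drop-outs:

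1. Remove the missing-completely-at-random assumption for GP uptake.
2. State the source of each uptake item, and report by arm the number of GPs randomised and the number with post-training uptake data.
3. Report the responders-only figure, and beside it a prespecified sensitivity analysis over all randomised GPs in which a GP with no post-training uptake data counts as a non-adopter. Where patient-reported items exist for a withdrawn GP, use them instead.
4. Note that the sensitivity figure is a bounding case, and that its between-arm difference can move either way if loss differs by arm.

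The cost is a change of wording, one extra table row and a possibly less favourable uptake figure. No extra GPs, patients or data collection are needed.

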### Data monitoring and adverse events

This study examines the efficacy of a GP training program and has no medium or high risk factors as defined by the Swiss Clinical Trial Organization (SCTO). Given the low-risk nature of the trial, monitoring will be performed internally at Unisanté by a member of our research support group. We will follow the guidelines for a low-risk monitoring strategy, as outlined by the SCTO. There will be a site initiation visit before inclusion of the first patient and at least one routine monitoring visit after inclusion of the first 2 to 5 patients.

Our intervention is a novel training program for general practitioners. We are measuring the efficacy of this training program and not the efficacy of a specific therapy or medication. All medications prescribed (ex: nicotine replacement therapy) and behavioural interventions administered (ex: advice for quitting and motivational interviewing) are already approved for use and recommended as standard of care in Switzerland. We will not inquire about adverse events or serious adverse events. Further, the information collected from patients is limited to smoking behaviours and does not include sensitive parts of their medical history or diagnoses. The decision aid is not considered a device requiring approval from Swissmedic because it does not make care recommendations or present personalized risk. The decision aid developed presents electronic cigarettes specifically as an option for quitting, as recommended by numerous experts [20] and approved by Swiss law [23].

### Ethics and dissemination

This study is conducted in compliance with the protocol, the current version of the Declaration of Helsinki, the principles of Good Clinical Practice, the Human Research Act (HRA, and the Human Research Ordinance (HRO) as well as other locally relevant legal and regulatory requirements. The Project Leader acknowledges his responsibilities as both the Project Leader and the Sponsor. Our protocol was accepted by the ethics commission of the canton of vaud in February 2021 (Project ID 2020–02,898).

### Protocol amendments

The original ethics approval was received 15.02.2021 for Version 1.2 of all study documents. Since then, we have made amendments to clarify blinding procedures (study staff are not blinded when contacting GPs and patients during follow-up), to clarify the monitoring plan, to allow patients to complete the consent and T0 questionnaire at home and return directly to the central study site, to specify how GPs can withdraw from the study. Approval for V1.4 was obtained 15.02.2022.

### Consent

At the level of GPs: Prior to the training program, GPs will receive an information sheet, complete a consent form and sign a contract outlining reimbursement of time spent in the training program and recruiting patients.

At the level of patients: Patient inclusion will occur at the GP office immediately prior to routine primary care visits. They will receive information materials about the study. If they tell the medical assistant or GP that they wish to participate, they will receive a consent form to sign and after that, will answer a screening questionnaire and a baseline questionnaire.

### Confidentiality

Coded data and participant identification lists will be stored separately. Trial and participant data will be handled with uttermost discretion and made only accessible to authorised personnel who require the data to fulfil their duties within the scope of the study. On the CRFs and other study specific documents, GP and patient participants are only identified by a unique participant number. The participant identification list that links identifying information to GP and patient study codes will be stored on the Unisanté server in a specific folder with access only for the PI and research assistants. The participant identification list will be deleted once patient recruitment and follow-up has been completed. Data from the Unisanté server are regularly backed up. Only allowed study members (doctors, statistician) and scientific collaborators and scientific collaborators with GCP training will have access to data. In case other members join the team (project managers, medical students), they might be given the right to access the data provided they have sufficient training.

### Access to data

Study data will be made publicly available after study completion and initial publication. Requests for study data can also be made by contacting [name] ([contact]).

### Dissemination policy

The proposed research is highly relevant to primary care physicians, policy makers, the general public and researchers interested in improving tobacco cessation in primary care patients. We hope to maximize implementation potential and determine how this intervention can be sustainably embedded in routine care.

The outputs from this study will be of interest to a wide variety of target audiences, ranging from patient and advocacy groups, healthcare professionals and healthcare organizations, to academics, the Swiss medical society (FMH) and the Federal office of public health, thus maximizing the potential for dissemination. We will work with each target audience to create dissemination and implementation strategies that are tailored to their needs and interests, understandable and pertinent to them. Since the intervention will be freely available, implementation in routine care could be rapid post project completion.

## Discussion

Smoking is the leading cause of preventable death in Switzerland. Adults who quit smoking between 25 and 34 years of age extend their life expectancy by 10 years [24]. Visits to a general practitioner are an opportunity to administer proven smoking cessation treatments, both pharmacologic and behavioural support, that can more than double a person’s chances of quitting successfully. The interventions, such as nicotine replacement therapy and motivational interviewing, have been shown in multiple studies to be safe and cost effective. However, currently few smokers get help with quitting smoking from their physician. We hypothesize that if GPs offer smoking cessation treatment as the default choice to all current smokers using an interactive decision aid, more smokers seen in primary care will quit smoking, as compared to usual care. We will randomly assign GPs to a training program teaching this new approach, which has been tested in the hospital setting and with pregnant women, but never in primary care. If we can improve smoking cessation counselling in primary care, we could have an important beneficial impact on public health.

Our study has several projected strengths, including its pragmatic design, which is very close to routine practice, and an intervention that should be easily implemented if successful. There is an important outcome for patients, which is smoking cessation. The cluster randomized design should also limit contamination between GPs. Our inclusion criteria for GPs and patients are broad so as to maximize the general usability of our results. The GPs who participate should be representative of GPs in private practice in French-speaking Switzerland. We are including poly-morbid and vulnerable patients. We are purposefully keeping our inclusion process brief to encourage less motivated patients to participate and limit co-interventions. A research assistant will follow-up with GPs to ensure they are enrolling patients correctly in the study. During the follow-up calls, we will not reinforce or discuss the concepts presented during the course. We will ensure that all patients are provided with an information sheet and the information that the study is optional.

This study presents several weaknesses, including an incomplete blinding and that the recruitment of patients is realized after the randomization of the GPs. We also use of self-reported smoking cessation at 6 months and not biochemical data to reduce the complexity of the study for the patients. Moreover, we are only intervening with GPs at one time point, and GPs may only see their patients once, such that the intervention may not be sufficiently strong to observe an effect. Another limitation is that the intervention includes two elements (the course and the electronic decision aid) and it will not be possible to know which of the two elements will have induced the most change.

However, we believe that this study has the potential to change significantly our approach to smoking cessation in primary care, and could have worldwide implications. The underuse of smoking cessation aids in primary care has been reported anecdotally and in the scientific literature in multiple countries. Default choices and the electronic decision aid are low-cost, easily diffusible interventions.

## Data Availability

Study data will be made publicly available after study completion and initial publication. Requests for raw data can also be made to [name] ([contact]). The decision aids are available free of charge at https://www.unisante.ch/fr/centre-medical/professionnels-sante/aides-decision.

## Abreviations

CO: Carbon Monoxide
CONSORT: Consolidated Standards of Reporting Trials
DA: Decision Aids
EU: European Union
GP: General Practitioner
MA: Medical Assistant
NRT: Nicotine Replacement Therapy
RCT: Randomized Controlled Trial
SDM: Shared Decision Making
UK: United Kingdom
USA: United States of America
